## Abstract

**Abstract:**

**Introduction:**

Some cancers are diagnosed late, making them harder to treat. People with an undiagnosed cancer may use over-the-counter medications to manage non-specific cancer-related symptoms that often mimic other more common, easily treatable conditions. Results from the original Cancer Loyalty Card Study (CLOCS) suggest there may be an increase in purchases of pain and indigestion medication 8–9 months before an ovarian cancer diagnosis. We aim to validate the CLOCS findings by exploring whether a significant change in medication purchases could be an indication for early signs of the following cancer types: oesophageal, stomach (gastric), colorectal (bowel), pancreatic, liver, bladder, endometrial, uterine sarcoma, ovarian and vulval, using data collected through store loyalty cards.

**Methods and analysis:**

Using a retrospective case-control design, we aim to recruit 1450 participants with one of the cancers of interest (cases) and 1450 participants without cancer (controls) in the UK who (or whose household members) hold a loyalty card with at least one participating high street retailer. We will use pre-existing loyalty card data to compare past purchase patterns of cases with those of controls. To assess cancer risk in participants and their purchasing patterns, we will collect information on demographic characteristics, health risk factors, lifestyle habits and behaviours, family history of cancer and any symptoms experienced prior to diagnosis (cases) and in the last year prior to study recruitment (controls). In addition, cases will be asked about their cancer diagnosis.

**Ethics and dissemination:**

CLOCS-2 was reviewed and approved by the East Midlands-Leicester South Research Ethics Committee (23/EM/0224). Study outcomes will be disseminated through peer-reviewed publications, conferences, presentations to the research communities as well as patients and the public, the study website and other social media outlets.

**Trial registration number:**

NCT06447064, CPMS58679; pre-results.

STRENGTHS AND LIMITATIONS OF THIS STUDYA key strength is the use of longitudinal purchase data recorded up to 6 years prior to enrolment, enabling analysis of temporal patterns before diagnosis.A further strength is the inclusion of multiple cancer types within a single study design, allowing comparison across groups.A key limitation is the incomplete capture of purchasing behaviour due to inconsistent loyalty card use and transactions outside participating retailers.Another limitation is the potential for exposure misclassification due to reliance on self-reported health survey data among cases and controls.

## Introduction

 Cancer is one of the leading causes of death worldwide, accounting for an estimated 9.6 million deaths each year.^1^ With significant advancements in cancer care and treatment, cancer-related deaths can be reduced when diagnosis and treatment occur at an early stage.^1^ However, for several major cancer types, diagnosis frequently occurs only after the disease has progressed, resulting in a poor prognosis.^2 3^

Early cancer diagnosis is essential to ensure timely treatment and improve patient outcomes.^4^,^6^ Unfortunately, delays can occur at any stage of the diagnostic spectrum/pathway, from the first observation of symptoms to the start of treatment. There are more than 200 types of cancer, each associated with different signs and symptoms. Some symptoms are disease-specific, whereas others are more general, such as weight loss, tiredness (fatigue) or unexplained pain which are often called non-specific cancer symptoms. The type of symptoms experienced can vary between individuals.^4^,^6^

In many cancers, patients may experience vague and/or non-alarming symptoms that resemble common illnesses, which could often seem to resolve or ease with the use of over-the-counter medications and home remedies.^4 7^ As a result, individuals may often self-care for their symptoms or seek advice from other sources such as from pharmacists, family or the internet, rather than from a general practitioner (GP).^8 9^ Common reasons for not presenting to the GP are the perception of “not wanting to waste the GP’s time” or because they have normalised their symptoms,^8 10^ not being able to make an appointment due to the lack of appointments available and looking for information online after not being able to make an appointment.^9^ For example, patients may downplay or normalise their symptoms, attributing them to something harmless, non-threatening or simply accept them as minor or everyday causes linked to their comorbidities.^11^ While persistence or worsening of symptoms, social influences and health literacy can encourage people to seek help from healthcare professionals, few believe their symptom(s) might actually be a sign of cancer until symptoms become persistent or debilitating.^9 12^

While advances in cancer care have been significant, the patient factors associated with earlier presentation to healthcare when individuals are experiencing symptoms are less understood.^11^ The Model of Pathway to Treatment stipulates that an individual’s symptom appraisal involves the evaluation of new symptoms, which is influenced by psychological, social and cultural factors, and may be through self-medication, symptom monitoring and changes in behaviour.^13^ Historically, research on these behaviours has been largely qualitative;^11^ however, more recent studies have begun exploring interventions to promote earlier help-seeking.^14^,^16^

In 2023, the findings from the Cancer Loyalty Card Study (CLOCS) offered a novel observational case-control study approach to test whether purchasing patterns captured through loyalty cards (store reward cards that record customers’ purchase histories) could provide early warning signals of ovarian cancer.^17^ The results showed that, compared with participants without ovarian cancer, those with ovarian cancer had a significant increase in purchases of indigestion and pain medications up to 9 months before a diagnosis of ovarian cancer was received (OR 1.38, 95% CI 1.04 to 1.83, p=0.03).^17^

Ovarian cancer was chosen to be the first type of cancer to be explored due to its non-specific symptoms and patient-reported experiences using the over-the-counter medication. Building on the findings of the original CLOCS, CLOCS-2 aims to validate these findings across ovarian cancer as well as nine additional cancers: oesophageal, stomach (gastric), colorectal (bowel), pancreatic, liver, bladder, endometrial, uterine sarcoma, ovarian and vulval cancers. These cancer types have been identified as cancers in which patients experience non-specific symptoms and self-care for^11^ and with highest gains in patient treatment outcomes and survival if diagnosed early.

A phased approach will be used. Four cancers (oesophageal, colorectal (bowel), pancreatic and ovarian), for which symptom profiles and patient pathways are better characterised, will be prioritised for full evaluation. The remaining six cancers will initially be piloted, as there is greater uncertainty regarding symptom presentation and the feasibility of recruitment within these groups. The pilot phase will inform the feasibility of wider inclusion of these cancers in the study.

If successful this study may lead to future interventions that might include sending an alert to individuals who exceed the ‘alert threshold’, advising them to visit a GP to discuss their symptoms, or delivering a potential public health message about purchase thresholds and the risks of self-treating potential cancer symptoms.

## Study objectives

The primary objective of this case-control study is to identify the time points at which participants with the following cancers (cases): oesophageal, stomach (gastric), colorectal (bowel), pancreatic, liver, bladder, endometrial, uterine sarcoma, ovarian and vulval, show statistically significant differences in their purchasing behaviours compared with purchase behaviours of participants without a cancer diagnosis (controls) over the previous 6 years. For controls, the purchases included are those recorded from participant consent to the study, up to a maximum of 6 years prior. For cases, the purchases included are those recorded up to the date of cancer diagnosis, to a maximum of 6 years, depending on when the diagnosis occurred. These behaviours include the purchase of items suspected of being used for symptom management (eg, painkillers, indigestion tablets) as well as changes in the frequency or quantity of other items purchased leading up to diagnosis. Participants’ historic loyalty card data will be collected from two major high street retailers.

The secondary objectives of CLOCS-2 are to: (1) Define a purchase threshold that may act as an “alert” for potential cancer symptoms in individuals and assess the predictive value of purchasing behaviours in the early detection of these cancers, (2) Develop a predictive model to determine the accuracy and efficacy of these purchasing behaviours for early cancer detection and (3) Create risk profiles from the participants’ self-reported health data and incorporate these into the analyses.

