#### Eligibility for cases

Men and women diagnosed and living with an eligible cancer type within the 2 years prior to the recruitment date are eligible to join the CLOCS-2 case-control study as cases. Patients’ usual care will continue to be provided by their usual healthcare professionals, and CLOCS-2 participation does not exclude patients from participating in other clinical or non-clinical studies.

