#### GP practices

After submitting an expression of interest, new RDNs or PCNs will receive further study information and set up an organisation information document (OID) for each participating GP practice. The OID developed with the North London RDN will serve as a template for other networks. A brief site initiation visit (SIV) will be held with each new RDN/PCN conducted by the CLOCS-2 team.

Clinical team members at each GP practice will identify potential study participants with a primary diagnosis of one of the eligible cancers, received in the last 2 years prior to recruitment date. Eligible cases will be randomly selected if the number of potential participants exceeds the required size. GP practices will match invited cases with eligible controls based on age bracket, sex and the number of inhabitants. Controls will be randomly sampled from participants without a cancer diagnosis who meet the matching criteria, typically selecting one control per case. Once eligible participants are identified, the GP practice will send a text message (drafted by the CLOCS-2 team).

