### Data sources and variables

#### Loyalty card data (for cases and controls)

CLOCS-2 participants or someone in their household will hold a loyalty card at one or both participating retailers that can be accessed by the UK population within all precincts, allowing the study to assess purchases of over-the-counter medications (ie, painkillers and indigestion medications) and eating habits. Eating habits will be used to identify dietary risk factors for specific cancers and to examine changes in dietary behaviour in response to potential cancer symptoms. The study will not include prescription-based pharmacy data which are not recorded in loyalty cards. After participants have provided consent, the CLOCS-2 team or the participant through the retailers’ OpenID platform (an interoperable authentication protocol that simplifies the way to verify the identity of users) will request their loyalty card data from the retailer, which will include individuals’ past purchase records from up to 6 years prior to the relevant cut-off date (study consent for controls or date of cancer diagnosis for cases). The purchase data will include each individual purchase, date of purchase, the location (ie, store postcode) and the product categorisation that is provided by the retailers. No additional individual information will be requested from the retailers.

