### Data extraction from the high street retailers

For both high street retailers, we will request up to 6 years in total of back-dated purchase data. The exact amount of data available for each participant will depend on how long they have had their loyalty card. Following participant consent, this data will be backdated from the date of study consent for controls or from the date of cancer diagnosis for cases.

The process for requesting data will differ between the two participating high street retailers. For Tesco, we will also use their Open ID Connect platform (figure 3). To facilitate this, a custom landing page was built which directs participants from REDCap to the retailer’s OpenID platform where participants will be able to sign in using their store login details. This ensures the retailer receives direct consent from the participants to share their loyalty card data with the CLOCS-2 research team. This approach eliminates the need for manual identity verification (eg, uploading ID documents), which was a barrier in the original CLOCS. It streamlines the process, reduces participant burden and improves data security by allowing the retailer to authenticate participants directly. It also ensures compliance with the retailer policies for sharing purchase data with third parties.

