**Figure 3 F3:**
[figure not shown]
Automated and manual process for obtaining loyalty card purchasing data from high street retailer(s) (a) Automated process showing secure data transfer between retailer (Tesco) and the CLOCS-2 research team following participant consent. (b) Manual process illustrating participant-mediated data sharing, including data request, download and submission steps.

For both participating retailers, a barcode ID will be generated for each primary registered cardholder by the CLOCS-2 team prior to transfer from Imperial College London to the high street retailer (figure 3). We will ask participants to provide their full name (as written on the loyalty card) and loyalty card number. The CLOCS-2 team will send the CSV file that contains a unique study ID, name of the individual and the exact loyalty card number specific to the retailer using the secure file transfer. The respective high street retailers will validate the participant information from the consent form and their loyalty card data from the health questionnaire. High street retailers will then centrally generate a dataset for all consenting individuals, in accordance with data sharing agreements, and will share participants’ past purchase data with the CLOCS-2 team for the period prior to the date of recruitment.

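### Case purchases are counted back from diagnosis and control purchases from consent, with no index date for controls, so calendar trends and season can appear as case-control differences

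*Protocol article*

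**What the plan says.** Study objectives sets the purchase windows. For controls: "For controls, the purchases included are those recorded from participant consent to the study, up to a maximum of 6 years prior". For cases: "For cases, the purchases included are those recorded up to the date of cancer diagnosis, to a maximum of 6 years", with a remark that the length depends on when diagnosis occurred. The data sections repeat these anchors: the cut-off is "study consent for controls or date of cancer diagnosis for cases" (Loyalty card data), and "this data will be backdated from the date of study consent for controls or from the date of cancer diagnosis for cases" (Data extraction from the high street retailers).

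Cases may join if "diagnosed and living with an eligible cancer type within the 2 years prior to the recruitment date" (Eligibility for cases). On matching, "GP practices will match invited cases with eligible controls based on age bracket, sex and the number of inhabitants" (GP practices). Calendar time is not a matching factor, and no section gives a control a reference date.

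Statistical methods describes two analyses. One is a conditional logistic regression with purchase proportion at various times before diagnosis as the exposure. It does not say how those times are defined for a control. The other is a set of Fisher's exact tests for each month before diagnosis, in which controls enter as their average monthly proportion over the observation period.

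Two places word the window differently. The strengths and limitations list refers to data recorded up to 6 years before enrolment. The text under Figure 3 says that retailers will share "past purchase data with the CLOCS-2 team for the period prior to the date of recruitment".

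**The concern.** The primary objective is to find the time points at which cases and controls differ in what they buy, so the time axis has to mean the same thing in both groups. Here it does not. For a case and control recruited together, the case's window ends 0 to 24 months before the control's. A gradual change in the share of target items, for example from product range or relative price, would then differ between the groups without any effect of cancer. Seasonal items raise a similar problem: a gap that is not a whole number of years compares different seasons, and a whole-period average smooths season out of the controls but leaves it in the case months.

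Matching on age bracket, sex and number of inhabitants cannot correct this. The alert threshold and the predictive model in the secondary objectives would inherit any artefact.

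**Working it through.** **Inputs from the protocol article.** Control anchor: consent. Case anchor: diagnosis. Maximum window: 6 years, or 72 months. Gap D from diagnosis to recruitment: 0 to 24 months. Recruitment starts on 4 February 2026 (Study timeline).

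**Assumptions, not in the documents.** There is no cancer effect. The target share changes by a constant relative rate g per year in both groups. D is uniform over 0 to 24 months (mean 12). Pair members consent at the same time and have full 72-month windows. The plan gives no figure of its own to reproduce on this point.

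**Overlap of windows.** Shared months = 72 − D:
- D = 0: 72 months (100%)
- D = 12: 60 months (83%)
- D = 24: 48 months (67%)

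The earliest control window starts in February 2020 (February 2026 less 6 years). A full case window can start in February 2018 (diagnosis in February 2024 less 6 years).

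**Regression, if control lags run back from consent.** Set the share at consent to 1. At lag L months, control share = (1+g)^(−L/12) and case share = (1+g)^(−(L+D)/12). The ratio is (1+g)^(−D/12) at every lag. Averaged over D uniform on 0 to 24 months, it is

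(1 − (1+g)^(−2)) / (2 ln(1+g)).

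For g = 5%: (1 − 0.9070)/(2 × 0.04879) = 0.953. For g = 2% and 10% it is 0.980 and 0.910. For g = −5% it is 1.053.

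**Monthly Fisher tests, control averaged over 72 months.** Control average = (1 − (1+g)^(−6)) / (6 ln(1+g)). For g = 5%: (1 − 0.7462)/(6 × 0.04879) = 0.867. The case share at lag L, averaged over D, is 1.05^(−L/12) × 0.953.

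| Lag (months) | Case share | Control average | Ratio |
|---|---|---|---|
| 1 | 0.949 | 0.867 | 1.09 |
| 9 | 0.919 | 0.867 | 1.06 |
| 24 | 0.864 | 0.867 | 1.00 |
| 60 | 0.747 | 0.867 | 0.86 |

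At lag 9 the ratio is 1.02 for g = 2%, 1.11 for g = 10% and 0.93 for g = −5%.

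**Where the Fisher bias vanishes.** For a fixed gap the ratio is approximately (1+g)^((36 − L − D)/12), because the 72-month average sits near month 36. It equals 1 at L = 36 − D: lag 36 for D = 0, lag 24 for D = 12 and lag 12 for D = 24.

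**With a common index date and equal-lag comparison.** D = 0 within the pair, so the ratio is 1.00 at every lag for any g. With g = 0 and no seasonality it is 1.00 under every scheme.

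**The case against.** The strongest reply is that the bias depends on something the documents do not report. It needs a trend or seasonal pattern in the target share itself. The exposure is a proportion of purchases, so a general change in card use or prices moves numerator and denominator together and largely cancels. About a year of ageing is small beside matching by age bracket. Seasonal effects partly cancel when diagnoses are spread over the year. The regression adjusts for confounders that the article does not list, and calendar time could be among them. All of this stands. It limits the size of the problem but leaves the anchors misaligned.

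Three stronger readings are tempting and should not be drawn.

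- **That every monthly comparison is biased, in one direction.** The same-lag ratio of 0.95 can apply only to the regression. The Fisher tests use a control average, so under the same rising trend the bias has the opposite sign near diagnosis, vanishes near lag 36 − D, and reverses at longer lags.
- **That the bias is a known fraction of the planned OR of 1.38.** The sample size section gives no exposure scale for that odds ratio, so a ratio of purchase shares cannot be set against it.
- **That the article gives two contradictory case windows.** The limits are worded as maxima, availability is said to vary by participant, and Study objectives already ends case purchases at diagnosis. The Figure 3 text describes what retailers transfer. This is loose wording to be tidied.

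**Conclusion.** The point holds as a design weakness that should be fixed before the final analysis. Different anchors, matching without calendar time and no control index date allow trend or seasonality in the target share to pass for a case-control difference in the primary time-point analysis.

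Under an assumed 5% a year rise and a uniform 0 to 24 month gap, the spurious ratio is about 0.95 in the regression (if control lags run from consent). In the Fisher tests it is about 1.09, 1.06 and 0.86 at lags 1, 9 and 60. The Fisher pattern deserves the most attention: a rise common to both groups would look like increased buying shortly before diagnosis, which is the signal sought and lies close to the 8 to 9 month lag reported from the original study.

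These sizes are illustrative. They scale with the trend, reverse sign if it is falling, and are zero if there is neither trend nor seasonality. In the regression the bias is also small for cases recruited soon after diagnosis. In the Fisher tests a short gap does not remove it, because the whole-period control average is itself misaligned.

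**What to change.** 1. Give each control the diagnosis date of its matched case as index date. Where no individual pair exists, draw a date from the case diagnosis dates in the same matching stratum. Controls must have been free of cancer (other than non-melanoma skin cancer) for 6 years before recruitment, so they remain valid controls at that earlier date.
2. Exclude control purchases after the index date, as is already done for cases after diagnosis.
3. Compare cases and controls at the same lag, and hence the same calendar month within a pair, in both the regression and the monthly tests. This replaces the whole-period control average in Statistical methods.
4. Use a common look-back of 48 months (72 − 24), which the control data already requested cover when pair members consent at about the same time. Each month by which a control consents later than its case can shorten this by a month. A longer look-back would need a longer control data request.
5. Align the strengths list and the Figure 3 text with the windows in Study objectives, Loyalty card data and Data extraction.

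The cost is a data-handling rule and revised wording, with no new participants. Up to the last 24 months of control purchases go unused, and the common look-back is shorter than the 6 years now described.

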## Methods and statistical analysis

We have completed the Strengthening the Reporting of Observational Studies in Epidemiology checklist, which is provided as online supplemental material S1.

